### Statistics

4.6

As this is an exploratory study, the sample size was not predetermined. However, a target of 100 participants for the cohort of medical staff, along with two groups of 25 participants each for the parent cohort has been set. The chosen sample sizes are justified based on feasibility considerations and the estimated response rates. Across the four study centers, an average of five new patients are admitted each month. All eligible patients and their parents who do not immediately decline participation will be included in the study. Based on prior experiences, it is estimated that approximately 50% of distributed questionnaires will be returned completed.

This corresponds to an expected return of around 2–3 questionnaires per month per center from the parents. With these projections, the parent cohort would reach the target size of 50 participants within approximately 6–8 months. For the cohort of medical staff, which is relatively stable in size, we anticipate achieving the target sample size within a similar period, assuming a participation rate of around 70%. A 95% confidence interval will be calculated for the proportion of participants who return completed questionnaires, allowing us to assess the precision of our estimates. This approach ensures that the sample size is sufficient to explore key outcomes while remaining realistic and aligned with the study's feasibility constraints.

The statistical analysis plan includes descriptive statistics for sample characteristics, feasibility, and effectiveness outcomes. Descriptive statistics comprise percentages for categorical variables and means with standard deviations for continuous variables. Feasibility results are analyzed by reporting the number and proportion of parents screened, enrolled, and counseled during the study period, along with retention and dropout rates. Reasons for dropouts are categorized and analyzed descriptively. Subgroup analyses explore variability across demographic groups, and qualitative interviews provide additional insights into perceived acceptability. For medical staff, feasibility is measured using the Feasibility of Intervention Measure (FIM), with descriptive statistics summarizing scores and qualitative interviews identifying barriers to implementation. Completion rates of planned counseling sessions are also reported descriptively, and differences across study centers are explored using chi-squared tests or Fisher's exact tests.

Effectiveness outcomes are analyzed by examining parental satisfaction with counseling, including clarity of information on complementary medicine (CM) and its safety, using the PS-CATE and SDM-Q-9 scales. Means and standard deviations are reported, and paired *t*-tests or Wilcoxon signed-rank tests are applied to compare satisfaction scores before and after the intervention. Changes in parents’ ability to make informed decisions are assessed through pre- and post-intervention scores on the SDM-Q-9. Changes in parental attitudes toward CM, as measured by the ABCAM, and perceptions of the benefits of potentially harmful CM procedures, as assessed with the I-CAM-R, are analyzed using paired t-tests for within-group comparisons. Between-group differences, such as those between intervention and baseline cohorts, are tested using independent t-tests or Mann–Whitney *U*-tests. For medical staff, training needs and perceived burden are assessed using Likert scales, while changes in knowledge, attitudes (CHBQ), and practices regarding CM are evaluated with paired *t*-tests. Subgroup analyses are performed to identify predictors of changes in these outcomes.

To ensure psychometric robustness, subscales of multi-faceted questionnaires are averaged into non-weighted indices by calculating the mean of individual items where applicable. Cronbach's alpha coefficients are computed to assess the internal consistency of scales. All statistical tests are exploratory and conducted at a significance level of alpha = 0.05, without adjustments for multiple testing. For significant changes, additional regression analyses are conducted to identify predictors of change in predefined outcomes such as satisfaction, attitudes, or decision-making ability. Qualitative data are analyzed using thematic content analysis to complement the quantitative findings. This comprehensive approach ensures a robust evaluation of the feasibility, acceptability, and effectiveness of the intervention while identifying potential areas for refinement.

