-Vestische Children's and Youth Hospital Datteln, Germany-Pediatric Hematology/Oncology, Dortmund Hospital, Germany-Department of Pediatrics and Adolescent Medicine, University Hospital Essen, Germany-Pediatric Hematology/Oncology, University Hospital Cologne, GermanyThe Rhine-Ruhr metropolitan area is beneficial for the fact that there are many oncological centers in a very small area, so that the treatment team can drive to them and deliver bedside counseling and support in presence. By selecting a prospective, multicenter study design, two cohorts of parents of children with a diagnosis of cancer and one cohort of medical staff from the participating pediatric oncology departments can be included. Sociodemographic data will be collected from all cohorts, with particular emphasis on the educational level of the parents, to determine whether education influences responses in the surveys. While one parent cohort will receive CM counseling, the other will serve as a waitlist cohort to be offered the respective CM counseling after the outcome assessment. Group assignment will be non-randomized by starting with a control cohort followed by the intervention cohort. After being informed about the study during the initial visit by their treating physician and signing written informed consent, parent cohorts will receive standard questionnaires three weeks after study inclusion. For the parent control cohort, the CM counseling will take place after this outcome assessment, while the parent intervention cohort will receive CM counseling before. Outcomes will be compared between groups. Medical staff will be trained in CM counseling strategies and assessed before and after the CM training. Outcomes will be compared within this group. A summary of the study design can be found in Figure 1. The active study period of recruiting is scheduled from December 2022 to end of 2027. Since there are five participating centers and a small project team, the time invested to be able to include subjects in the study will be in relation to the effort involved. For the medical staff, 100 participants are considered an acceptable and desirable number. Traveling to the study centers and maintaining contact with parents requires resources. The sample size for the survey and consultation includes 50 participants, evenly divided into two cohorts of 25 individuals each. We also expect a dropout of 10%, as parents who find themselves in such a difficult situation might also turn away.

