### Limitations

5.2

A further task is to ensure the compliance of the parents as well as the medical staff. Parents whose children have cancer face an emotional challenge and may find it difficult to engage with the trial. Studies show that an informed patient influences treatment-related expectations and patient engagement (46, 47). In addition, the parents are already burdened with substantial documentation and paperwork related to conventional studies, consent forms, and various other requirements. For this reason, solid communication skills and authentic empathy are required on the part of project staff (48), and the project team has been specifically trained to meet these demands. At the same time, hospital staff have many patients and therefore little time for additional activities. Compliance and commitment of both groups is maintained through close, personal contact in the form of educational talks as well as the possibility of telephone feedback. In addition, counseling and support will take place on site at the respective facility and strengthen engagement.

A possible effect could be that participants tend to respond in a socially desirable way, knowing that the study deals with attitudes and acceptance towards CM. To minimize this bias, we will ensure anonymity, stress the absence of right or wrong answers, ask neutral questions, and include implicit honesty prompts. Additionally, indirect questioning techniques will be used where appropriate to reduce socially desirable responses. These measures aim to encourage participants to disclose their true opinions and behaviors. Furthermore, a generalization of the results of the evaluation to Germany as a whole may be limited, as five out of 62 study centers in Germany will participate (8%). With regard to the generalizability of the results of the evaluation, it should be mentioned that individuals who are interested in CM may be more likely than other to participate in the survey. However, it could also be useful for people who have a rather positive attitude towards CM to be informed about its safe use. The need to improve communication about CM in pediatric oncology is also underlined by other authors (48).

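### The parent cohorts are compared on returned questionnaires only, at an expected return of about half, and counseling comes before the form in one cohort only, so who returns it could differ by cohort

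*Protocol article*

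**What the plan says.** The Statistics section of the protocol article takes in nearly everyone at the start: "All eligible patients and their parents who do not immediately decline participation will be included in the study". It then expects a large loss: "it is estimated that approximately 50% of distributed questionnaires will be returned completed". From this it derives "an expected return of around 2–3 questionnaires per month per center from the parents" and concludes that "the parent cohort would reach the target size of 50 participants within approximately 6–8 months". The parent target is thus counted in returned forms.

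Under Outcomes, each parent cohort fills in one questionnaire. Study setting and design gives it to both cohorts at three weeks, but the order of counseling differs. Intervention parents are counseled first, whereas "For the parent control cohort, the CM counseling will take place after this outcome assessment". Assignment is sequential and not randomized.

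The Statistics section says that between-group differences, "such as those between intervention and baseline cohorts, are tested using independent t-tests", with the Mann–Whitney test as the alternative. A 95% interval is planned for the proportion returning the form, and dropout rates and reasons are to be described. The Primary outcome section words the questionnaire hypotheses as the influence of the project on satisfaction, decision-making, attitudes and stress.

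Two other figures bear on the same loss. Study setting and design expects 10% dropout, and Data analysis requires at least 80% retention.

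**The concern.** With one form per parent, a non-returner contributes no outcome and has no earlier score to stand in for it. (The Statistics section also names paired tests for parents, but the Outcomes section provides no earlier parent measurement.) The between-cohort test therefore compares returners with returners.

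That is harmless only if return works in the same way in both cohorts. Here the intervention comes before the form in one cohort and not in the other. A parent who has had a bedside session may be readier to answer, or may answer only if the session was welcome. A control parent still waiting for counseling has a different motive. The Limitations section concedes that people interested in complementary medicine may be likelier to take part, but treats this as a limit on generalizability. Such interest lies close to the attitude and use outcomes, so the same selection could enter the cohort comparison.

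The risk is that a difference produced by who answers is reported as an influence of counseling. This is separate from the lack of randomization: two perfectly comparable enrolled cohorts could still differ among their returners.

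**Working it through.** **The plan's own figure.** Inputs from Statistics: five new patients a month, 50% return. Read per center, 5 × 0.50 = 2.5 a month, which matches the stated 2–3. The sentence "Across the four study centers, an average of five new patients are admitted each month" could also mean five in total, but only the per-center reading gives that figure.

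**How many parents go unobserved.** For 25 returned forms per cohort, 25 / 0.50 = 50 must be handed out per cohort, or 100 in all. On the literal wording, as many included families are unobserved as observed.

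**Size of a possible bias.** Neither the dependence of return on outcome nor the return by cohort is in the documents, so both are assumed. Let the outcome be standard normal with no true cohort difference. A parent returns the form when a latent propensity, correlated ρ with the outcome, passes the cut that gives return rate p. The mean among returners is then shifted by ρ × φ(z_p) / p.

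- p = 0.40: φ/p = 0.3863 / 0.40 = 0.966
- p = 0.60: φ/p = 0.3863 / 0.60 = 0.644
- Difference between cohorts: 0.322 × ρ, which is 0.10 SD at ρ = 0.3 and 0.16 SD at ρ = 0.5

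If higher scorers return more (ρ positive), the cohort with the lower return is inflated more. If ρ is negative, the sign reverses. The direction is therefore open.

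| Return, control v intervention | ρ, control v intervention | Absolute shift (SD) | Type I error of the t-test |
|---|---|---|---|
| 50% v 50% | 0.3 v 0.3 | 0 | 4.9% |
| 40% v 60% | 0.3 v 0.3 | 0.10 | 6.3% |
| 50% v 50% | 0 v 0.3 | 0.24 | 13% |

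The error rates come from 20,000 simulated trials with 50 forms handed out per cohort, tested two-sided at 0.05. The last row shows that equal return rates alone do not rule out bias, because the kind of parent who returns can still differ.

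**Scale.** With 25 per cohort, the standard error of the difference is √(2/25) = 0.28 SD, and the difference detectable with 80% power is about 0.79 SD. A shift of 0.10 to 0.16 SD is therefore 0.3 to 0.6 of one standard error.

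**If the loss is smaller.** Post-inclusion loss of 10% in one cohort and 20% in the other, taken from the dropout and retention figures, gives (0.350 − 0.195) × ρ = 0.155 × ρ, or 0.05 to 0.08 SD at ρ = 0.3 to 0.5.

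**The three loss figures side by side.** 50% return, 10% dropout (90% remaining) and at least 80% retained cannot all describe the same loss. If a non-returner counts as lost, the expected 50% fails the 80% criterion. If not, the article does not say what dropout and retention count.

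**The case against.** The strongest reply is that this belongs to an analysis plan. Return by cohort and comparison of returners with non-returners are details that an article may leave out. This stands in part. A reader might infer that only one pooled return figure will be reported and that the record data will go unused for non-returners. The article says neither; it is silent. The point rests instead on what is stated: the expected return, the single form, the order of counseling and the unadjusted test.

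A reader might also take the Limitations sentence, "Compliance and commitment of both groups is maintained through close, personal contact", as evidence of unequal contact between cohorts. It is not, because the two groups there are parents and hospital staff. Both cohorts get the form at the same time, the telephone hotline is open to study participants generally, and controls still have counseling to come. Nothing in the documents shows that return will differ.

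The 50% is also ambiguous. The step from five new patients to 2–3 returns leaves no separate allowance for refusal, so it may cover the whole path from admission to returned form. Loss after inclusion would then be smaller. The literal wording speaks of distributed forms, and the conflict with the other figures remains either way.

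Finally, the tests are exploratory, the article says under Strengths that the questionnaires give only a direction, and no progression criterion uses a cohort difference. Sequential assignment already weakens attribution. This limits the consequence. It does not cancel it, because the hypotheses are worded as influence and the Statistics section claims a robust evaluation of effectiveness.

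**Conclusion.** The concern holds as a risk that the stated design creates, not as a demonstrated bias. About half of the distributed parent forms are expected to be missing, non-returners have no outcome, and counseling precedes the form in one cohort only. Selection among returners could therefore differ by cohort because of the intervention.

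Direction and size are unknown. The 0.10 to 0.16 SD rests on an assumed correlation of 0.3 to 0.5 and an assumed 40% v 60% return. It is zero if return rate and selection are the same in both cohorts, and larger if selection differs in kind. The tempting stronger reading, that every cohort comparison is biased by a known amount, is not supported by the documents. For an exploratory study the consequence lies in how results may be worded, and that is reason enough for a cheap correction.

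**What to change.** - Compute the planned return proportion and its 95% interval separately for each cohort. With 25 of 50 returned, the exact interval runs from 36% to 64%, so the absence of a clear difference does not show equal return.
- Compare returners with non-returners, by cohort, on diagnosis, age and center from the records already being collected.
- Keep hand-out and reminders the same in both cohorts. This has to be settled during data collection, as it cannot be recovered afterwards.
- If return or returner characteristics differ between cohorts, describe the results as differences among returners and do not attribute them to counseling.
- Reconcile the 50% return with the 10% dropout and the 80% retention criterion by stating what each figure counts and over which denominator.

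Weighting for the probability of return is at most an optional sensitivity analysis. It is imprecise with 50 parents, and weights built on diagnosis, age and center do not remove return that depends on the outcome itself.

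The cost is a little more analysis and a more cautious conclusion. No new measurements are needed.

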1.Is it feasible to recruit a sufficient number of parents/medical staff to obtain representative cohorts?2.Is it feasible to implement CM interventions in different conventional study centers according to the protocol or are there barriers that will require protocol adjustments?Secondary objectives include exploratory outcomes for evaluation:
1.Do trained parents feel better informed about the risks, benefits and safety of CM compared to untrained parents, and does this increase their ability to make better informed decisions about their use of CM?2.Do attitudes towards CM and CM usage differ between trained and untrained parents?3.To what extent does the medical staff feel relieved from administrative tasks, time pressure, and professional uncertainty by the external provision of CM counseling for parents?4.Can knowledge of the benefits and risks of CM among medical staff and their attitudes towards it be improved?The results should make it possible to successfully implement and establish CM counseling and supporting strategies in conventional pediatric cancer centers. In addition, individual CM counseling concepts will be developed for other clinics in the long term, in order to meet evidence-based IM recommendations (6).

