## Outcomes

4

All participants will be asked about baseline social demographics. Data on pediatric cancer characteristic will be obtained from medical records. Both cohorts of parents receive one questionnaire each, while medical staff receive questionnaires twice, once before and once after the CM training (see Figure 2). The questionnaires refer to the objectives already mentioned above in the protocol.

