Additionally, compliance will be assessed by ensuring that at least 80% of planned counseling sessions are completed, while any barriers to implementation, such as logistical or organizational challenges, will be identified through qualitative interviews with staff. Data quality is another essential criterion, with at least 90% of collected questionnaires expected to be complete and analyzable to ensure the reliability of feasibility and outcome measures. Finally, satisfaction rates among parents and medical staff regarding counseling content and delivery will be monitored, and specific barriers to implementation will be identified through semi-structured interviews.

These criteria provide a structured basis for determining the feasibility of the intervention and whether it warrants further investigation in a fully powered randomized controlled trial (RCT). If certain criteria are not met, modifications may be made, and feasibility reassessed in subsequent phases.

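### Section 4.6 words the parent PS-CATE/SDM-Q-9 outcome as satisfaction with counseling, which control parents have not had from the project when they answer; sections 4.2 and 4.3 word it as satisfaction with information on CM, and the sections must be reconciled

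*Protocol article*

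**What the plan says.** **Timing.** Under Study setting and design (3.1), "parent cohorts will receive standard questionnaires three weeks after study inclusion". The cohorts differ in what precedes that form: "For the parent control cohort, the CM counseling will take place after this outcome assessment", whereas the intervention cohort is counseled first. The same section adds "Outcomes will be compared between groups".

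**Number of measurements.** The opening of Outcomes (4) states "Both cohorts of parents receive one questionnaire each". Only medical staff are measured twice.

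**What is measured.** Statistics (4.6) says "Effectiveness outcomes are analyzed by examining parental satisfaction with counseling, including clarity of information on complementary medicine (CM) and its safety", and names PS-CATE and SDM-Q-9 as the scales. Evaluation (4.2) assigns the same two instruments to satisfaction with the CM information provided and to the ability to make informed decisions. The hypotheses in Primary outcome (4.3) also speak of satisfaction with information.

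**Objective.** Secondary objective 1 asks "Do trained parents feel better informed about the risks, benefits and safety of CM compared to untrained parents", and whether this helps them decide.

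**Tests.** For the satisfaction scores, section 4.6 names a paired t-test or Wilcoxon signed-rank test, before against after. For decision ability it refers to SDM-Q-9 scores before and after the intervention. A later sentence, which does not name these scales, reads "Between-group differences, such as those between intervention and baseline cohorts, are tested using independent t-tests", with Mann–Whitney U as the alternative.

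**The concern.** Satisfaction with a counseling service can be rated only by someone who has received it. If section 4.6 is followed literally, counseled parents rate the project session. The article does not say what uncounseled parents rate: some other conversation, the absence of one, or nothing. A higher score in the counseled cohort could then mean that those parents are better informed, or only that they had a session to rate.

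Two of the four hypotheses in section 4.3 rest on these scales (satisfaction with information, ability to decide), as does secondary objective 1. Section 4.6 also sends significant changes in satisfaction and decision-making into regressions for predictors, so an ambiguous outcome would carry over into that step.

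**Working it through.** The protocol gives no effect size, standard deviation (SD) or power for PS-CATE or SDM-Q-9, so there is no stated figure to reproduce. The check is a comparison of sections.

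**1. Can control parents rate the outcome at their only assessment?**

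| Section | Outcome as worded | Can an uncounseled parent rate it? |
|---|---|---|
| 4.2 Evaluation | satisfaction with CM information provided; ability to decide | yes, from whatever information they have |
| 4.3 Primary outcome | satisfaction with CM information; ability to decide | yes |
| 2 Objectives, secondary objective 1 | feeling informed, counseled against uncounseled | yes; this is the intended contrast |
| 4.6 Statistics | satisfaction with counseling | not for a project session |

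The first three rows agree; section 4.6 is the exception. Feasibility (4.1) shows the rule applied correctly elsewhere: the AIM, which rates the intervention itself, is limited to the parent intervention cohort. Section 4.6 sets no such limit.

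**2. Which comparison can be run?** A paired test needs two scores per parent. Section 4 gives one questionnaire per parent, so there are no pairs in either cohort. The remaining comparison is intervention against control at week 3. Section 3.1 states it for outcomes in general, secondary objective 1 asks for it, and section 4.6 supplies the tests. That it applies to these two scales is an inference from those sections; section 4.6 does not say so directly.

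**3. Does usual care give control parents something comparable to rate?** For information, yes: the Introduction lists relatives, practitioners, online media and other parents as sources. For a conversation with a professional it is less sure. The centers have no in-house specialized CM counseling (Objectives), only about half of parents tell their oncologist about CM use, and oncologists often do not ask (Introduction). The number of control parents with such a conversation is not given and could be anywhere from 0 to 25.

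**4. Scale of the comparison.** Assume a two-sided alpha of 0.05 (sidedness is not stated), a normal approximation and SD = 1. The difference detectable with 80% power is (1.960 + 0.842) × √(1/n₁ + 1/n₂).

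- 25 against 25: 2.802 × √(2/25) = 0.79 SD.
- After the 10% dropout in section 3.1, 22.5 per cohort: 2.802 × √(2/22.5) = 0.84 SD.
- With 25 per cohort, power is about 18% at 0.3 SD, 42% at 0.5 SD and 81% at 0.8 SD.

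A shift caused only by the lack of a session to rate would therefore usually reach significance only at about 0.8 SD or more. The documents give no size for such a shift.

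**The case against.** The strongest reply is that one phrase in section 4.6 is being set against the rest of the document. Sections 4.2 and 4.3 and secondary objective 1 all point to information, and the section 4.6 sentence itself goes on to mention clarity of information. Poor satisfaction with CM information among uncounseled parents is what a waitlist control is meant to show. The AIM restriction shows that the authors saw that controls cannot rate the session. All tests are exploratory, and section 5.1 says the questionnaire outcomes only give a direction. Most of this stands, and it is why the point is a conflict of wording with consequences for interpretation and not a failed endpoint.

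It does not remove the point. The analysis section carries the one wording that fails in half the parents, and the article does not say what control parents are asked to rate.

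Two further replies:

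- The PS-CATE and SDM-Q-9 items are not shown, so whether they presuppose a consultation, or offer a not-applicable answer, cannot be settled here. This stands. It is therefore unsupported to say that controls must leave items blank, score low or rate something else.
- Section 4.3 has a sentence that could be read as before-and-after data for parents as well as staff. Section 4 is explicit that parents have one form, and section 3.1 describes a single assessment. If the control cohort is meant as the before state (section 4.6 speaks of a baseline cohort), the two samples are different parents and a paired test is still wrong.

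**Conclusion.** The point holds as an inconsistency that should be corrected. Under the section 4.6 wording, a difference between parent cohorts on PS-CATE or SDM-Q-9 could not be separated from having had a session to rate. Under the wording of sections 4.2 and 4.3 it can be interpreted as the planned contrast, subject to the non-randomized, sequential allocation. Two of four hypotheses and 25 of 50 planned parents are affected. The paired parent tests in section 4.6 cannot be run on the data described. The conclusion assumes that section 4 is right about one questionnaire per parent.

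Two stronger readings are not supported:

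- A reader might infer that any difference between cohorts is produced by the schedule. It is not, if parents rate information: counseled against uncounseled at week 3 is then the intended comparison.
- A reader might infer that the data-quality criterion, "at least 90% of collected questionnaires expected to be complete and analyzable", is bound to be threatened. If all 25 control parents left the scales blank, parent completeness would be 25/50 = 50%. Pooled with 2 × 100 staff forms it would be (250 − 25)/250 = 90%. Both figures need every control parent to leave the scales blank, one blank scale to spoil a whole form, and every planned form to be collected. The documents say none of these, so the figures are a worst case and carry no weight here.

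**What to change.** 1. In section 4.6, replace satisfaction with counseling by *satisfaction with information on CM*, in line with sections 4.2 and 4.3.
2. Report any rating of the counseling session itself in counseled parents only, descriptively and without a test between cohorts, as section 4.1 does for the AIM.
3. Analyse the parent PS-CATE and SDM-Q-9 scores by the between-cohort tests already named, and delete the paired tests for these parent scores.
4. State one object of rating for both cohorts, in identical wording: CM information, or CM conversations, so far and from any source. Add a *no such conversation* answer and report its proportion in each cohort.

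**Cost.** Items 1 to 3 change text only. Item 4 needs a lead-in sentence and a tick box, and is cheap only if both cohorts get the same form. Controls are enrolled first and recruitment is scheduled from December 2022, so control forms may already exist. If so, keep the wording they used for both cohorts and state the limitation; changing it for the intervention cohort alone would add a new difference between them.

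Some control parents may have no SDM-Q-9 score. As an illustration, if half of them had no CM conversation (an assumption), the detectable difference rises from 0.79 SD to 2.802 × √(1/12.5 + 1/25) = 0.97 SD. The controls who remain are those who had such a conversation and may be more interested in CM, so the SDM-Q-9 comparison should be read beside the proportion with no conversation.

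### Section 4.6 plans paired, before-and-after analyses of four parent scales, but each parent completes one questionnaire, so only the between-cohort comparison can be run

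*Protocol article*

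**What the plan says.** **Schedule.** Section 3.1 of the protocol article (Study setting and design) says that "parent cohorts will receive standard questionnaires three weeks after study inclusion". It then separates the cohorts by when counseling falls: "For the parent control cohort, the CM counseling will take place after this outcome assessment, while the parent intervention cohort will receive CM counseling before". For parents, "Outcomes will be compared between groups"; for medical staff, who are assessed before and after training, "Outcomes will be compared within this group". Section 4 (Outcomes) confirms the number of assessments: "Both cohorts of parents receive one questionnaire each, while medical staff receive questionnaires twice, once before and once after the CM training". What it states for baseline is that "All participants will be asked about baseline social demographics", with cancer characteristics taken from the medical records. It states no baseline outcome scale for parents.

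**Analysis.** Section 4.6 (Statistics) takes parental satisfaction (PS-CATE and SDM-Q-9) and states that paired t-tests or "Wilcoxon signed-rank tests are applied to compare satisfaction scores before and after the intervention". Decision-making ability is to be assessed from SDM-Q-9 scores before and after the intervention. ABCAM and I-CAM-R "are analyzed using paired t-tests for within-group comparisons". Where a change is significant, regressions are to look for its predictors, with satisfaction, attitudes and decision-making ability as examples. One further sentence provides unpaired tests (independent t-test or Mann–Whitney) between the intervention cohort and what it calls the baseline cohort, without saying which scales it covers.

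**The concern.** A paired test or a change score needs two values from the same person. The schedule gives each parent one. The tests that section 4.6 attaches to the four named parent scales therefore have no data, and neither do the regressions on predictors of change in parents.

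This matters because section 4.3, headed Primary outcome, lists satisfaction with information, decision-making ability and attitudes among the hypotheses to be tested. Whoever analyzes the parent data will have to depart from the printed plan for these outcomes, and the plan does not say clearly what replaces it. The word change also invites a before-and-after claim about parents that the data cannot support.

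**Working it through.** The plan gives no figure to reproduce here. The check is a count of measurements per parent against what each test needs.

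**Inputs**
- Parents: 50, as two cohorts of 25 (sections 3.1 and 4.6).
- Questionnaires per parent: 1, three weeks after inclusion (sections 3.1 and 4).
- Control cohort: counseled after that questionnaire (section 3.1).
- Intervention cohort: counseled before it (section 3.1).
- Questionnaires per staff member: 2, before and after training (section 4).

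**Count for any one parent scale, with full response**

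| Group | Score before counseling or training | Score after | Complete pairs |
|---|---|---|---|
| Parent control cohort (25) | 25 | 0 | 0 |
| Parent intervention cohort (25) | 0 | 25 | 0 |
| All parents (50) | 25 | 25 | 0 |
| Medical staff, own scales (target 100) | 100 | 100 | 100 |

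Complete parent pairs = 0 + 0 = 0 of 50. The 25 scores before counseling and the 25 after it come from different families.

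**Each parent analysis in section 4.6 against the count**

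| Analysis | Needs | Can it be run? |
|---|---|---|
| PS-CATE and SDM-Q-9, paired t or Wilcoxon signed-rank | 2 values per parent | No |
| SDM-Q-9, scores before and after | 2 values per parent | No |
| ABCAM and I-CAM-R, paired t | 2 values per parent | No |
| Regression on predictors of change, parent outcomes | 2 values per parent | No |
| Unpaired test between cohorts | 1 value per parent, two groups | Yes, 25 v 25 |

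The one analysis that can be run is the one the rest of the article leads the reader to expect. Section 2 (Objectives) frames the parent questions as trained against untrained parents, and section 3.1 reserves the within-group comparison for staff.

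**The case against.** **A runnable parent analysis is already in the plan.** This is the strongest reply, and it stands. Section 4.6 names unpaired tests between the cohorts. A reader might infer from the paired wording that the plan has no workable parent effectiveness analysis. That goes too far: a between-cohort difference can be estimated, and what is lost is within-parent change. The sentence follows the attitude scales, however, and is not tied to PS-CATE or SDM-Q-9, while the paired analyses are tied to named scales.

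**Parents may be assessed twice after all.** Section 4.3 speaks loosely of interviewing the parent cohorts and staff before and after the training. ABCAM and I-CAM-R also appear under both 4.1 and 4.2. The phrase can refer to staff alone, to the qualitative interviews, or to the two parent cohorts taken together. Listing a scale under two headings does not create a second occasion. Neither overrides the explicit count of one questionnaire in section 4. If two assessments are intended, the error lies in sections 3.1 and 4, and the text still has to be reconciled.

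**The full protocol or analysis plan may settle it.** It may, but this is not something the article leaves out. It states both the tests and a schedule that rules them out.

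**The study is exploratory.** The main objective is feasibility and acceptability, none of the progression criteria in section 4.5 uses a paired parent test, and section 5.1 says the questionnaire outcomes only indicate a direction. This limits the consequence. It does not supply data for a test that has none, and section 4.3 gives the affected outcomes some prominence.

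**Two further inferences are tempting but unsupported.** One is that analysts will pair unrelated control and intervention families and so obtain wrong standard errors. Section 4.6 assigns unpaired tests to exactly that comparison, so this is speculation. The other is that satisfaction cannot be rated before counseling. Section 4.2 defines the outcome as satisfaction with the information provided on complementary medicine, which uncounseled parents can rate.

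**Conclusion.** The contradiction is real and limited to the parent outcomes. On the printed schedule, the paired tests and before-and-after scores for all four named scales (PS-CATE, SDM-Q-9, ABCAM, I-CAM-R) have 0 of 50 pairs, and regressions on change in parents have no outcome variable. The between-cohort comparison of 25 v 25 remains possible. The paired analyses of medical staff are unaffected.

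This rests on one assumption: that sections 3.1 and 4 describe the parent schedule correctly. It does not depend on effect size, power or dropout. The plan makes no power claim for these tests, and power figures would not measure this defect.

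It should be corrected before analysis, because named tests for hypotheses listed under Primary outcome cannot be carried out as written. A reader should not infer that the feasibility and acceptability conclusions fall with it; the stated progression criteria do not use these tests.

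**What to change.** 1. In section 4.6, delete the paired tests and the before-and-after wording for parents.
2. State one analysis for each of PS-CATE, SDM-Q-9, ABCAM and I-CAM-R in parents: the difference between cohorts in the three-week score, with a 95% confidence interval. The unpaired tests already named can accompany it.
3. In sections 4.2 and 4.6, replace change with difference between cohorts wherever parents are meant.
4. Keep the paired tests and the regressions on predictors of change for medical staff only.
5. If parents are in fact assessed before and after counseling, correct sections 3.1 and 4 to say so instead of making changes 1 to 4.

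Changes 1 to 4 cost only wording; no data collection changes. The price is in what can be claimed. There will be no statement about within-parent change, and because the cohorts are sequential and non-randomized, the difference between them must not be reported as change.
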